## Abstract

**Background:**

Metabolic syndrome (MetS) affects approximately one-third of community-dwelling older adults (≥65 years) and is characterized by concurrent dysregulation of glucose and lipid metabolism alongside chronic low-grade inflammation. Poor long-term adherence to conventional omega-3 supplementation has prompted interest in sustainable, food-based delivery systems. Omega-3 polyunsaturated fatty acid (PUFA)-enriched eggs—produced through dietary modification of hen feed to enhance eicosapentaenoic acid (EPA) and docosahexaenoic acid (DHA) content-represent a palatable and easily incorporated dietary vehicle for sustained intervention.

**Methods:**

This is a three-arm, parallel-group randomized controlled trial that will enroll 180 community-dwelling adults aged ≥ 65 years with MetS. Participants will be randomly allocated (1:1:1) to receive either omega-3 PUFA-enriched eggs, regular eggs, or no egg intervention (usual diet) for 12 weeks. Those assigned to the egg intervention groups will consume one boiled egg daily, five days per week. The control group will maintain their habitual dietary patterns without additional egg consumption. Biological samples (blood, urine, and stool) will be collected at baseline and weeks 4, 8, and 12. Plasma concentrations of omega-3 fatty acids, lipid metabolism indicators,inflammation and oxidative stress markers will be measured. Exploratory outcomes include comprehensive multi-omics profiling, encompassing metabolomics and gut microbiome will be tested.

**Results:**

The primary outcome will be the longitudinal changes in fasting triglycerides (TG) measured at Weeks 0, 4, 8, and 12, with comparisons between the omega-3 PUFA-enriched eggs group and the regular eggs control group. Secondary outcomes will include glucose levels, insulin concentrations, lipid profiles, as well as biomarkers of inflammation and oxidative stress. Integrative multi-omics analyses will be conducted to explore the pathways linking omega-3 PUFA-enriched eggs consumption to alterations in metabolomic features and gut microbiota.

**Conclusions:**

This trial will aim to assess the efficacy, feasibility, and mechanisms of omega-3 PUFA-enriched eggs in elderly adults with MetS, so as to provide insights and evidence to support scalable community-based dietary interventions.

**Trial registration:**

The protocol has been registered on the website of Chinese Clinical Trial Registry. The Identifier code is ChiCTR2600120125. The Registry date is 10 March, 2026. Registry name is “Interventional Effect of ω-3 Polyunsaturated Fatty Acid-Fortified Eggs on Elderly Patients with Metabolic Syndrome.” Registration URL is [https://www.chictr.org.cn/bin/userProject].

## Introduction

1

Metabolic syndrome (MetS), one of the most prevalent chronic disorders worldwide, is a clinical entity characterized by central obesity, hypertension, dysglycemia, elevated triglycerides, and reduced high-density lipoprotein cholesterol (1). Its core pathophysiological characteristics include insulin resistance, disordered glucose and lipid metabolism, and concomitant low-grade chronic inflammation (2). The prevalence of metabolic syndrome (MetS) remains high among community-dwelling older adults aged 65 years and older, and is associated with elevated risks of cardiovascular disease, type 2 diabetes mellitus, and physical functional decline. Furthermore, chronic low-grade inflammation, as reflected by increased high-sensitivity C-reactive protein (hsCRP), frequently coexists with MetS and multidimensional frailty. This indicates that disordered glucose and lipid metabolism coupled with chronic inflammation may constitute a key common pathway underlying adverse clinical outcomes in older adults with MetS (3). With global aging accelerating, identifying effective, safe, and easily implementable intervention strategies for metabolic syndrome has become an urgent public health and clinical research priority.

Omega-3 polyunsaturated fatty acids (PUFAs), mainly eicosapentaenoic acid (EPA) and docosahexaenoic acid (DHA), have been extensively investigated for their potential in mitigating metabolic risk. They exert beneficial effects by regulating lipid metabolism, enhancing insulin sensitivity, and mediating strong anti-inflammatory responses (4, 5). Numerous observational studies and clinical trials have demonstrated that increased omega-3 PUFA intake is associated with improvements in individual components of metabolic syndrome. Mechanistically, omega-3 PUFAs may modulate multi-level network interactions across lipidomic, transcriptomic, inflammatory signaling, microbiomic, and metabolomic pathways, thereby affecting lipid synthesis and transport (6). Systematic reviews and meta-analyses of randomized controlled trials have consistently demonstrated that marine-derived omega-3 supplementation results in triglyceride (TG) reductions in a dose- and duration-dependent manner among individuals with metabolic syndrome. Nevertheless, the beneficial effects on high-density lipoprotein cholesterol (HDL-C), blood pressure, and fasting blood glucose remain inconsistent, largely attributable to heterogeneity across studies and limited sample sizes (7). Traditional omega-3 supplementation largely depends on fish oil capsules or increased consumption of fatty fish. EPA and DHA are primarily derived from marine sources, whereas the *in vivo* conversion efficiency of plant-derived α-linolenic acid (ALA) to EPA and DHA is limited. Furthermore, the average dietary intake of EPA and DHA is merely 0.067 g/day (0.03%E), which is far below the recommended daily intake of 0.25–2.00 g/day for omega-3 polyunsaturated fatty acids (8). Such a gap poses substantial challenges to achieving effective dietary exposure levels. Moreover, elderly individuals frequently encounter compliance barriers including taste, odor, cost, swallowing difficulties, gastrointestinal intolerance, and poor long-term adherence, which considerably restrict the broad practical application of such interventions (9–11). Therefore, the key challenge lies in identifying a sustainable, palatable dietary vehicle that can effectively integrate omega-3 interventions into daily dietary practice.

Therefore, it is critical to identify a practical dietary vehicle capable of efficiently delivering omega-3 PUFAs while supporting long-term adherence. This objective may be effectively achieved through the use of omega-3 PUFA-enriched eggs, which are produced by adjusting the diet of laying hens to elevate the content of EPA and DHA (12). Eggs are widely accepted, convenient to consume, and represent a staple in daily diets, rendering them an ideal “invisible” carrier for omega-3 polyunsaturated fatty acids. This strategy is highly consistent with the dietary habits of older adults, supports standardized production and monitoring, and may enhance the feasibility and long-term adherence of interventions. Recent studies have showed that intake of omega-3 PUFA-enriched eggs effectively elevates plasma omega-3 fatty acid concentrations and improves lipid profiles in healthy adults (13–15). In addition, a double-blind randomized controlled trial reported that three months of continuous consumption of omega-3 PUFA-enriched eggs (also fortified with omega-5 and omega-7 fatty acids) significantly reduced waist circumference among individuals at risk of metabolic syndrome, suggesting potential benefits against central obesity—a core phenotypic feature of MetS (16).

Nevertheless, current evidence remains limited in several aspects. First, most existing studies on omega-3–enriched eggs have focused on general adult populations or individuals at metabolic risk, with a lack of high-quality evidence among elderly patients with confirmed metabolic syndrome. This makes it difficult to draw reliable conclusions regarding the true intervention effect in this clinically important subgroup (16). Second, some studies focus on conventional clinical endpoints, including serum lipid and glucose concentrations, yet mechanistic research remains insufficient. While the metabolic benefits of omega-3 fatty acids have been associated with lipid remodeling, inflammatory regulation, and gut microbiota alterations, human trial findings remain inconsistent, accompanied by marked interindividual variability. A recent large-scale double-blind randomized controlled trial among patients with type 2 diabetes and hypertriglyceridemia demonstrated that fish oil supplementation significantly lowered triglyceride levels and remodeled the serum lipidome, while producing only minimal effects on overall gut microbiota composition. Notably, baseline gut microbiota profiles strongly predicted triglyceride-lowering responses, with partial mediation by specific lipid metabolites. These observations indicate that the microbiota–metabolite–clinical phenotype regulatory pathway warrants further validation in populations with metabolic syndrome (17). Finally, the interactions between omega-3 polyunsaturated fatty acids and gut microbiota, as well as their metabolites such as short-chain fatty acids, have emerged as a key mechanistic framework underlying the health benefits of omega-3 supplementation (18). However, systematic evaluations of omega-3 PUFA-enriched egg interventions focusing on gut microbiota and host metabolome regulation in elderly patients with MetS remain scarce. Therefore, a rigorously designed and practically feasible clinical trial is urgently needed to bridge the gap between clinical evidence and mechanistic insights.

This study primarily hypothesized that regular consumption of omega-3 PUFA-enriched eggs by elderly patients with MetS could improve glucose and lipid metabolism and chronic inflammation compared to those consuming regular eggs (control intervention group) or receiving no intervention (blank control group). The underlying mechanisms involve remodeling of lipid metabolic pathways, alterations in gut microbial composition, and changes in key metabolite profiles. This study aimed to investigate the impact of omega-3 PUFA enriched eggs on markers of glycemic and lipid metabolism (e.g., TG, HDL-C, fasting blood glucose, and insulin resistance) and inflammatory indicators in elderly MetS patients. It further aimed to examine changes in gut microbial composition and associated clinical metabolic phenotypes following intervention. Additionally, this study sought to identify key metabolites altered by omega-3 PUFA-enriched egg consumption and establish a multi-omics framework to clarify variations in intervention effectiveness. Finally, by integrating omics data with pathway analysis, this study aimed to explore potential biological mechanisms underlying the metabolic benefits of omega-3 PUFA-enriched eggs in elderly individuals with MetS.

This study will primarily hypothesize that consumption of omega-3 PUFA-enriched eggs by elderly patients with MetS will improve glucose and lipid metabolism and chronic inflammation, compared with those who consume regular eggs or receive no intervention (blank control group). The underlying mechanisms will involve remodeling of lipid metabolic pathways, alterations in gut microbial composition, and changes in key metabolite profiles. This study will aim to investigate the impact of omega-3 PUFA-enriched eggs on markers of glycemic and lipid metabolism and inflammatory indicators in elderly MetS patients. It will further aim to examine changes in gut microbial composition and associated clinical metabolic phenotypes following the intervention. Additionally, this study will seek to identify key metabolites altered by omega-3 PUFA-enriched egg consumption and establish a multi-omics framework to clarify variations in intervention effectiveness. Finally, by integrating omics data with pathway analysis, this study will aim to explore potential biological mechanisms underlying the metabolic benefits of omega-3 PUFA-enriched eggs in elderly individuals with MetS.

## Methods

2

### Study hypothesis

2.1

This study hypothesizes that sustained, regular consumption of omega-3 PUFA-enriched eggs in elderly adults with MetS will improve glucose and lipid metabolism and attenuate chronic low-grade inflammation. The underlying mechanisms are postulated to involve remodeling of lipid metabolic pathways, modulation of gut microbial ecology, and alterations in key metabolite profiles.

### Study design

2.2

This study is designed as a three-arm, parallel-group randomized controlled trial that will recruit 180 older adults with MetS. Eligible participants will be randomized equally to: (i) omega-3 PUFA-enriched egg intervention; (ii) standard egg control; or (iii) usual-diet control, with a 12-week follow-up period. Post-intervention outcomes will assess the impact of enriched eggs on MetS indicators and elucidate mechanistic pathways. This protocol is registered with the WHO International Clinical Trials Registry Platform (Table 1).

**Table 1 T1:** Items from the world health organization international clinical trials registry platform data set.

Item	Information
**Registration number**	ChiCTR2600120125
**Date of registration**	2026-03-10
**Registration status**	Prospective registration
**Public title**	Interventional Effect of ω-3 Polyunsaturated Fatty Acid-Fortified Eggs on Elderly Patients with Metabolic Syndrome
**Scientific title**	Interventional Effect of ω-3 Polyunsaturated Fatty Acid-Fortified Eggs on Elderly Patients with Metabolic Syndrome
**Name of the ethic committee**	Institutional Review Board of Peking University
**Approved No. of ethic committee:**	IRB00001052-25192
**Date of approved by ethic** **committee**	2026-01-05
**Study type**	Interventional Study
**Study design**	Parallel, a three-arm, parallel-group randomized controlled trial
**Objectives of study**	To determine the effects of 12-week omega-3 PUFA-enriched egg consumption on glucolipid metabolism, gut microbiota composition, and systemic metabolomic profiles, and to elucidate the underlying integrative mechanisms in older adults with metabolic syndrome.
**Key inclusion and exclusion criteria**	Inclusion Criteria: Community-dwelling adults aged ≥65 years with a clinical diagnosis of metabolic syndrome. Exclusion Criteria: Medical Conditions: Severe hepatic or renal impairment, immunodeficiency disorders, active infectious diseases, or type 1 diabetes; malignant hypertension, malignancy, thyroid dysfunction (hyperthyroidism or hypothyroidism), or electrolyte disturbances; acute diabetic complications or severe chronic complications, including cardiovascular or cerebrovascular events, within the preceding month; prior bariatric surgery or recent significant weight change (unintentional or intentional loss >5% over 3 months or >10% over 6 months). Dietary Factors: adherence to specialized therapeutic diets (e.g., gluten-free for celiac disease) or any substantial dietary modification within 12 weeks prior to enrollment. Cognitive and Functional Status: severe medical or psychiatric disorders, or cognitive, visual, or hearing impairments that would preclude study compliance. Medication and Supplement Use: current use of omega-3 PUFA supplements (fish oil, omega-3 fatty acids, DHA, EPA, or ALA) or medications known to affect lipid metabolism. Concomitant medication use is systematically documented during the screening visit via a comprehensive medication questionnaire, capturing all prescription and over-the-counter drugs and supplements, including product names and duration of use. Allergies: documented egg allergy.
**Interventions**	Group1: Omega-3 PUFA-enriched eggs group Intervention: Participants will consume one omega-3 PUFA-enriched egg daily, five days per week (Tuesday through Saturday). Monday and Sunday are designated as egg-free days, during which no eggs or egg-derived products are permitted. Concurrent use of deep-sea fish oil and other omega-3 fatty acid supplements is prohibited throughout the intervention period. Group2: Regular eggs group Intervention: Participants will consume one regular egg daily, five days per week (Tuesday through Saturday). Monday and Sunday are designated as egg-free days, during which no eggs or egg-derived products are permitted. Concurrent use of deep-sea fish oil and other omega-3 fatty acid supplements is prohibited throughout the intervention period. Group3: blank control Group Intervention: Participants will maintain their habitual dietary patterns throughout the 12-week study period. Consumption of deep-sea fish oil and other omega-3 fatty acid supplements is prohibited for the duration of the trial.
**Outcomes**	Plasma concentrations of omega-3 fatty acids, lipid metabolism indicators,inflammation and oxidative stress markers; metabolomics and gut microbiome
**Collecting samples**	Blood, Urine, Fecal samples
**Recruitment state**	Not yet recruiting
**Randomization procedure**	The randomization sequence will be generated by an independent statistician ([name], Peking University School of Public Health) who is not involved in trial conduct or outcome assessment. Using simple randomization, participants will be allocated in a 1:1:1 ratio to one of three group: (i) omega-3 PUFA-enriched eggs intervention; (ii) regular eggs group; or (iii) blank control group. Randomization will be performed via the sample() function in R software (version 4.3.1). The sequential allocation list will be encrypted and stored in a secure, access-controlled repository. To ensure allocation concealment, the randomization schedule will remain inaccessible to intervention administrators, outcome assessors, and data analysts until the completion of data collection and the prespecified unblinding procedure.
**Blinding**	An open-label control with blinded intervention arms design will be adopted in this study. Of the three randomly allocated groups, only the blank control group will be unblinded and aware of their non-intervention status. The control group and the omega-3 PUFA-enriched eggs group will be administered using a blinded protocol, where participants will be informed that they will receive egg intervention but will remain blinded to the specific type (regular fresh eggs vs. omega-3 PUFA-enriched eggs). Blinded personnel will also include intervention administrators, outcome assessors, and data analysts. Throughout the entire trial, intervention administrators, outcome assessors, and data analysts will be informed only of the unique identification codes of the participants and will be unaware of the intervention types corresponding to each group. The random allocation table will be encrypted and stored in a secure, access-controlled repository by an independent third-party biostatistician, and centralized unblinding will be performed only after the trial has been completed and the data have been locked.
**Data collection and management**	Data will be collected using paper-based or electronic Case Report Forms (CRFs). The content of the CRFs will cover modules including participants' baseline characteristics, intervention implementation status, outcome indicator test results, and adverse event records. All data entries will be completed by trained researchers to ensure the authenticity, accuracy, and completeness of the data. A standardized Electronic Data Capture (EDC) system will be used for data collection and management, and the specific system to be used will be finalized prior to trial initiation.

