### Study participants

2.4

Participants will be recruited from Guangyang District, Langfang City, Hebei Province, using purposive and convenience sampling methods. Recruitment strategies will include community health clinic screenings, health education sessions, and telephone invitations.

Inclusion Criteria: Community-dwelling adults aged ≥ 65 years with a clinical diagnosis of MetS will be included. MetS will be defined as meeting at least three of the following five criteria: (i) abdominal obesity: waist circumference ≥90 cm (men) or ≥85 cm (women); (ii) hyperglycemia: fasting plasma glucose ≥6.1 mmol/L or 2-h post-load glucose ≥7.8 mmol/L on oral glucose tolerance test (OGTT), or previously diagnosed diabetes currently under treatment; (iii) elevated blood pressure: systolic blood pressure ≥130 mmHg and/or diastolic blood pressure ≥85 mmHg, or previously diagnosed hypertension currently under treatment; (iv) hypertriglyceridemia: fasting triglycerides ≥1.70 mmol/L; and (v) low high-density lipoprotein cholesterol: fasting HDL-C < 1.04 mmol/L.

Exclusion criteria: (i) medical conditions—severe hepatic or renal impairment, immunodeficiency disorders, active infectious diseases, type 1 diabetes, malignant hypertension, malignancy, thyroid dysfunction, electrolyte disturbances, acute diabetic complications or severe chronic complications (including cardiovascular or cerebrovascular events within the preceding month), prior bariatric surgery, or recent significant weight change (>5% over 3 months or >10% over 6 months); (ii) dietary factors—adherence to specialized therapeutic diets or substantial dietary modification within 12 weeks prior to enrollment; (iii) cognitive and functional status—severe medical or psychiatric disorders, or cognitive, visual, or hearing impairments that would preclude study compliance; (iv) medication and supplement use—current use of omega-3 PUFA supplements or medications known to affect lipid metabolism (concomitant medication use will be systematically documented during the screening visit via a comprehensive medication questionnaire); and (v) allergies—documented egg allergy.

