### Intervention initiation and follow-up data collection

3.5

Intervention week 0 (first day of Week 2): During the baseline week, structured questionnaires will be administered to assess dietary intake, psychological status, sleep quality, physical activity, cognitive function, medical history, and concomitant medication and supplement use. Trained physicians will perform standardized anthropometric measurements, including height, weight, waist circumference, blood pressure, and body composition. Participants will be instructed to collect midstream urine samples from the first morning void using clean, sterile disposable containers, which will be transferred to pre-labeled urine collection tubes for storage and subsequent analysis. Fresh stool samples will be self-collected in sterile containers and delivered to research personnel for gut microbiota and metabolomic analyses. Fasting antecubital venous blood samples will also be obtained for outcome assessment. Participants will complete and submit three-day dietary records for verification. They will then receive eggs corresponding to their randomized group allocation, along with a “Participant Diary” for daily recording of egg consumption, supplement use, and medication intake. Diary entries and video documentation of egg consumption will be uploaded to a secure online platform to enable real-time monitoring and compliance verification by research staff. Community physicians will evaluate chronic disease complications and intercurrent symptoms based on physiological parameters, with detailed documentation of onset times, treatments, and durations to facilitate subsequent data analysis.

Intervention Weeks 4, 8, and 12: Follow-up assessments will mirror the Week 0 procedures. Fasting antecubital venous blood samples will be collected by trained medical personnel at each visit.

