Participants who require medical treatment, initiate lipid-lowering therapy, or experience acute illness or exacerbation of chronic conditions during the intervention period will have the onset time, duration, and treatment measures documented in detail. Dietary assessments and other measurements will be scheduled within prespecified time windows for each study phase to minimize potential confounding effects. The study flowchart is presented in Figure 1. The schedule for enrollment, intervention, follow-up, and assessment is shown in Table 2. The intervention components and responsible personnel for the study are summarized in Table 3.

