(1) Glucose metabolism and insulin resistance indicators: Measured markers will include fasting plasma glucose (FPG), glycated hemoglobin (HbA1c), fasting insulin, and C-peptide to assess glycemic control and pancreatic β-cell function. Additionally, the homeostasis model assessment of insulin resistance (HOMA-IR) will be calculated as: HOMA-IR = [FPG (mmol/L) × FINS (mU/L)] ÷ 22.5, where higher values indicate greater insulin resistance.(2) Metabolomics: This study will employ untargeted metabolomics to characterize the systemic effects of omega-3 PUFA-enriched egg intervention on metabolic phenotypes, aiming to identify potential metabolic pathways and biomarkers associated with primary clinical outcomes. Plasma, urine, and stool samples will be collected at baseline (Week 0) and follow-up visits (Weeks 4, 8, and 12), then stored at −80 C pending analysis. Metabolite features will be detected using liquid chromatography-mass spectrometry (LC-MS). To ensure reproducibility, standardized protocols adhering to the Minimum Reporting Standards for Metabolomics and Chemical Analysis Reporting Elements will be implemented throughout sample preparation, instrument operation, metabolite annotation, identification, and data preprocessing (26). Additionally, quality control samples will be incorporated to monitor analytical drift and batch effects, with corrections applied as needed to enhance data quality and comparability (27). Metabolomic results will provide exploratory mechanistic insights, which will be interpreted in conjunction with clinical phenotypes and findings from other omics analyses.(3) Gut microbiomics: Gut microbiota-related indicators will be evaluated as exploratory mechanistic outcomes to elucidate potential gut-derived mechanisms underlying metabolic phenotype changes (e.g., triglycerides) in older adults with metabolic syndrome following omega-3 PUFA-enriched egg intervention. Primary microbiome measures will include α-diversity, β-diversity, community structure comparisons, and analyses of differential microbial abundance and functional pathways.

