Stool samples will be collected at baseline (Week 0) and at Weeks 4, 8, and 12, and then stored at−80 C for subsequent analysis. The primary analytical endpoint will align with the clinical outcomes (Week 12), while samples collected at Weeks 4 and 8 will be analyzed to explore temporal changes and potential mechanisms. To ensure reproducibility and comparability, all procedures—including sample collection, storage, DNA extraction, sequencing, and statistical analyses—will follow standard operating procedures and reporting guidelines for human stool sample processing (28, 29).

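### Gut microbiota composition is in the registered objective, but the medication exclusion covers only lipid-related products, so recent antibiotic use can add avoidable noise to the exploratory stool outcomes

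*Protocol article*

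**What the plan says.** The objective in Table 1 of the protocol article (section 2.2) is "To determine the effects of 12-week omega-3 PUFA-enriched egg consumption on glucolipid metabolism, gut microbiota composition, and systemic metabolomic profiles". Section 5.4 gives the rank of the microbiome measures: "Gut microbiota-related indicators will be evaluated as exploratory mechanistic outcomes". It also gives the sampling times: "Stool samples will be collected at baseline (Week 0) and at Weeks 4, 8, and 12", with week 12 as the main microbiome time point.

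The medication and supplement exclusion appears twice. Table 1 has "current use of omega-3 PUFA supplements (fish oil, omega-3 fatty acids, DHA, EPA, or ALA) or medications known to affect lipid metabolism". Section 2.4, item (iv), has "current use of omega-3 PUFA supplements or medications known to affect lipid metabolism". Neither list mentions antibiotics or probiotics. The on-trial prohibition in Table 1 and section 3.3 likewise covers only omega-3 supplements. The nearest other criterion excludes people with a current infection.

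Exposure data are collected. Table 1 describes a screening questionnaire on all medicines and supplements, with product names and how long each has been used. Section 3.5 provides a diary "for daily recording of egg consumption, supplement use, and medication intake", and says that participants who need treatment or fall acutely ill "will have the onset time, duration, and treatment measures documented in detail".

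**The concern.** The exclusion is written for the lipid part of the objective and not for the microbiota part. Section 2.4 sets the criteria out in five numbered classes, so the gap is not simply the result of Table 1 listing key criteria only. A person whose infection has resolved and who finished antibiotics the week before enrolment meets every criterion as written. Their week-0 stool then serves as the reference for weeks 4, 8 and 12.

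Baseline stool matters to this trial on its own account. The Introduction cites a fish-oil trial in which overall microbiota composition hardly moved while the baseline profile predicted the triglyceride response. The expected signal may therefore be small, and the baseline is itself an explanatory variable in the network the Discussion hopes to build. At stake is the precision of the exploratory microbiome, stool-metabolome and microbiome-metabolome results.

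**Working it through.** **Inputs from the protocol.** Section 2.3 gives σ = 58 mg/dL, δ = 35 mg/dL, two-sided α = 0.05, 80% power and 25% dropout. No microbiome sample size or power is stated, and no rate or effect of antibiotic exposure.

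**The plan's own figure.** With σ² in the numerator (the printed formula omits it), n = 2 × (1.96 + 0.84)² × 58² / 35² = 43.06, rounded up to 44. Then 44 / 0.75 = 58.7, rounded up to 59 and set at 60 per arm. This reproduces, but it concerns triglycerides only. It is used here solely to obtain the number left after dropout: 60 × 0.75 = 45 per arm.

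**Assumed inputs (not in the documents).** A share p of stool samples is shifted by d between-person standard deviations on some diversity or abundance measure, with the same p in each arm. The range taken is p = 5% to 20% and d = 1 to 2.

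**Formulas.**
- Variance ratio V = 1 + p(1 − p)d².
- Loss of effective sample size = 1 − 1/V.
- Reference effect with 80% power at 45 per arm: (1.960 + 0.842) × √(2/45) = 0.59 SD.
- Power, noise only = Φ(2.802/√V − 1.960).
- Power if the intervention effect is also lost in exposed samples = Φ(2.802(1 − p)/√V − 1.960).
- Number per arm to restore 80% (noise only) = 45V, rounded up.
- SD of the chance between-arm difference due to exposure = d√(2p(1 − p)/45).

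| p | d | V | Effective-n loss | Power, noise only | Power, effect also lost | Per arm for 80% | SD of chance imbalance |
|---|---|---|---|---|---|---|---|
| 5% | 1 | 1.05 | 4.5% | 78% | 74% | 48 | 0.05 |
| 10% | 1.5 | 1.20 | 17% | 72% | 63% | 55 | 0.09 |
| 10% | 2 | 1.36 | 26% | 67% | 58% | 62 | 0.13 |
| 20% | 2 | 1.64 | 39% | 59% | 42% | 74 | 0.17 |

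The expected between-arm difference from exposure is zero in every row, because p is the same in each arm under randomisation.

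**Limit of the calculation.** The formula describes one measure at one visit. In a four-visit comparison the effect depends on how many of a person's samples are exposed and on the within-person correlation, neither of which is given. The table shows scale and is not a forecast.

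**The case against.** The strongest reply is that this concerns an exploratory outcome in a community trial, that arms are randomised concurrently, and that medication is recorded throughout. Most of it stands, and it rules out several stronger readings that a reader might reach.

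- *That every stool sample will be analysed whatever the exposure.* Section 7 is silent; it states no such rule. The Discussion says that data from participants who cease to meet the criteria are dropped, which could reach a current infection though not antibiotic use as such. Section 5.4 refers stool handling and analysis to procedures not shown. Handling rules of this kind may also sit in an unseen analysis plan, so their absence here is no finding.
- *That recovery after antibiotics could pass for an intervention effect.* For the comparison between arms, it could not do so systematically. Inference rests on group by time against concurrent randomised arms. Recovery enters the common time effect in expectation, leaving noise and chance imbalance.
- *That an exposed baseline is beyond repair.* Recorded exposures can be flagged, adjusted for or set aside. What remains is narrower: the questionnaire is framed around concomitant use, so a course completed before screening is not clearly captured, and the diary starts only when eggs are handed out.
- *That any probiotic user distorts change from baseline.* A stable daily probiotic is a constant exposure. Only starting or changing one resembles a transient disturbance.
- *That antibiotic recovery outweighs anything an egg could do.* The documents give no figure for either.

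The reply does not remove the mismatch between the objective and the exclusion. Eligibility is fixed in the protocol and decided at enrolment.

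**Conclusion.** The point holds as a minor, inexpensive improvement in precision. Followed as written, the protocol admits people whose baseline stool may be disturbed by a recent systemic antibiotic course, although microbiota composition is part of the registered objective. The consequence is extra variance, dilution and chance imbalance in the exploratory microbiome and stool-metabolome comparisons. Systematic bias between arms is not expected, and the primary triglyceride comparison is not affected.

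The size is unknown. Under the assumed range it runs from negligible (4.5% of effective sample size) to material (39%), and the upper figure is the extreme corner of that range, with both inputs at their highest.

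**What to change.** 1. Before recruitment starts (Table 1 lists the trial as not yet recruiting), add to Table 1 and section 2.4(iv) an exclusion for recent systemic antibiotic use and for newly started or changed probiotic use. The investigators should set the look-back; the 12 weeks already applied to dietary change is one consistent option.
2. Have the screening questionnaire ask explicitly about courses completed within that window.
3. Use the diary and treatment records of section 3.5 to flag stool samples taken after on-trial antibiotics, and repeat the microbiome and stool-metabolome analyses without them.

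Postponing the baseline stool until the window has passed is not a workable substitute, because section 3 allows one baseline week before the intervention.

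The cost is one eligibility line, one questionnaire item and one further run of exploratory analyses. The downside is slightly fewer eligible volunteers and a smaller sample set in the restricted run.
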